### Procedure and Materials

#### Intervention

The intervention participants will receive the full version of the Thrive program, comprising a 1-hour web-based presentation each week for 7 weeks. Each presentation will be a webinar (web-based seminar) delivered via the Zoom platform (Zoom Video Communications Inc). Participants will view the webinars as prerecorded videos on a dedicated webpage, which will ensure uniform delivery of the intervention. Each webinar will be copresented by 2 members of the research team. One presenter (MM) is a Nurse Educator from the hospital with a Master’s degree in Adult Education and extensive experience in providing professional development courses to health care workers. The other presenter ([name]) is a researcher from the [name] Group at Neuroscience Research Australia (NeuRA) and the University of New South Wales (UNSW) with a PhD in Psychology and extensive experience in lecturing, tutoring, and counseling.

Each webinar will follow a 3-step sequence named *Inform, Inspire, Improve*. The *Inform* and *Inspire* sections will last approximately 25 minutes each, and the *Improve* section will last approximately 10 minutes. During the *Inform* section, the presenters will share scientific findings from the fields of neuroscience, medicine, and psychology to educate the participants on the links among brain health, mental well-being, and one of the 7 areas of life covered by the program. This section will provide knowledge only, as a background to the subsequent sections. During the *Inspire* section, the presenters will provide advice, guidance, and recommendations on how to improve one’s brain health and mental well-being in the relevant area of life. This section will build upon the preceding knowledge by offering practical suggestions to implement in one’s daily life. Finally, during the *Improve* section, the webinar viewers will have an opportunity to reflect on the knowledge and suggestions shared in the preceding sections, and they will be invited to commit to enacting at least one of the suggestions in their own lives.

The knowledge and recommendations provided in each webinar are based on peer-reviewed empirical studies from the medical and behavioral sciences, with a special emphasis on neuroscientific findings. The webinars also draw upon other authoritative sources such as the US Department of Health and Human Services, the Australian Government National Health and Medical Research Council, and the World Health Organization. The full reference list for the Thrive program contains >250 peer-reviewed publications, and the participants will be provided with a reference list for each week of the program in case they wish to check anything or explore the literature themselves. Textbox 1 provides an overview of the program content for each of the 7 webinars.

Overview of the Thrive webinar content for the intervention group.
**Webinar topics and content**
Week 1 (sleep): impact of sleep quantity and quality on well-being and the brain; tips for improving sleep quality in relation to light exposure, exercise, meal timing, and nutrition; cognitive behavioral tips for sleeping better; and accessing treatment for a sleep-related disorderWeek 2 (exercise): impact of physical activity on well-being and the brain; tips for increasing motivation to exercise in relation to social connection, natural environments, and novelty or variety; using the internet to find new ways to exercise; exercising in a way that suits one’s personal preferences; and how to access an exercise physiologist through the publicly funded health care systemWeek 3 (nutrition): impact of nutrition on well-being and the brain; links among nutrition, human evolution, and chronic noncommunicable diseases; tips for improving one’s diet in relation to avoiding empty calories, practicing mindful eating, and accommodating dietary restrictions; and how to get tested for micronutrient deficienciesWeek 4 (stress management): impact of stress on well-being and the brain; how the stress system works; tips for managing and reducing stress using mindfulness, controlled breathing, and effective coping strategies; and how to access treatment for posttraumatic stress disorder or a stress-related disorderWeek 5 (social connection): impact of social connections on well-being and the brain; tips for improving connections using compassionate communication, active listening, nonverbal communication, and acts of kindness; and how to use the internet to make new social connectionsWeek 6 (cognitive challenge): impact of cognitive challenge on well-being and the brain; tips on challenging oneself using new knowledge, linguistic or mathematical puzzles, skill development, and novelty; and how to overcome anti-intellectual stigma and follow one’s curiosityWeek 7 (life purpose and meaning): impact of life purpose on well-being and the brain; the differences between hedonia and eudaimonia; the state of flow and how to achieve it; and tips for achieving a greater sense of purpose and fulfillment by targeting character strengths and weaknesses, setting meaningful goals, accepting unavoidable hardship, and identifying one’s core values

Each week, in addition to the reference list, the intervention participants will receive a 1-page *reflective sheet* and a 4-page infographic summary. The reflective sheet will prompt participants to write down their key learning from that week’s webinar, what this learning means to them, and what they will do next to act on it. After viewing each webinar, the participants will be encouraged to fill in their reflective sheet and add it to their CPD portfolio, although this is not a requirement to complete the program. The infographic document will provide a summary of the *Inform* section of that week’s webinar (ie, a summary of the neuroscience and other background information covered in the webinar).

#### Active Control

The active control participants will receive an extremely reduced version of the Thrive program. In each of the 7 weeks, they will be emailed the infographic summary on that week’s topic and instructed to read it. The infographic documents will be identical to those received by the intervention participants. In short, the control participants will be provided with only the *Inform* section for each week’s topic, in the form of the infographic summary only. They will not receive any tips and advice for promoting well-being. Thus, the intervention participants will receive knowledge plus practical advice and reflective opportunities (in webinar and document forms), whereas the control participants will receive knowledge only (in document form only). The control participants will receive a reference list to accompany each infographic summary, but they will not receive the reflective sheets. To summarize, each week, the intervention participants will receive a webinar, reflective sheet, infographic, and reference list, whereas the active control participants will receive the infographic and reference list only.

### Survey Measures

#### Overview

A range of questionnaires will be administered via the web-based surveys, but not all will be administered at each measurement occasion (see Table 1 for an outline of the questionnaire timings).

**Table 1 table1:** Questionnaires delivered at each time point.

Questionnaire	Survey 1 (week 0)	Survey 2 (week 4)	Survey 3 (week 8)	Survey 4 (week 12)
Demographics	✓			
Medical history	✓			
Health and lifestyle	✓	✓	✓	✓
COMPAS-W^a^	✓	✓	✓	✓
RRC-ARM^b^	✓			
DASS-21^c^	✓	✓	✓	✓
Abbreviated POMS^d^	✓	✓	✓	✓
Brief COPE^e^	✓	✓	✓	✓
Self-Compassion Scale	✓			✓
Compassion Scale	✓			✓
MAAS^f^	✓			✓
HPQ^g^ (work performance items)	✓			✓
UWES^h^	✓			✓
DLE^i^ (trauma items)	✓			
DLE (COVID-19 items)	✓	✓	✓	✓
COVID-19 Exposure Survey	✓	✓	✓	✓
Thrive attendance items		✓	✓	✓
Thrive satisfaction items			✓	✓

^a^COMPAS-W: Composure, Own-worth, Mastery, Positivity, Achievement, and Satisfaction for Wellbeing Scale.

^b^RRC-ARM: Resilience Research Centre Adult Resilience Measure.

^c^DASS-21: Depression, Anxiety, and Stress Scale–21-item version.

^d^POMS: Profile of Mood States.

^e^COPE: Coping Orientation to Problems Experienced.

^f^MAAS: Mindful Attention Awareness Scale.

^g^HPQ: Health and Work Performance Questionnaire.

^h^UWES: Utrecht Work Engagement Scale.

^i^DLE: Daily Life Events.

#### Demographics

This questionnaire will measure age, sex, education, occupation, and other demographic characteristics.

#### Medical History

This questionnaire will ask whether the participant or anyone in their immediate family has ever been diagnosed with a learning or developmental disorder or diagnosed with and treated for a psychological or psychiatric disorder.

#### Health and Lifestyle

This questionnaire will ask about health-related habits, including questions on diet, exercise, sleep, and drug and alcohol use.

#### COMPAS-W Scale

The COMPAS-W scale [4] is a 26-item questionnaire that measures overall mental well-being as well as the six subcomponents of Composure, Own-worth, Mastery, Positivity, Achievement, and Satisfaction. Each item presents a statement with a 5-point response scale ranging from *strongly disagree* to *strongly agree*. The respondents are asked to answer the items in terms of how they feel *most of the time* but, in this study, the instructions will be modified for the second, third, and fourth surveys to ask the respondents how they have felt *over the past month* (ie, since taking the previous survey).

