### Sample Size

Power calculations suggest that at least 200 participants need to be recruited (100 per condition) to detect a small group-by-time interaction effect at 80% power. This sample size was calculated using the statistical software package G*Power (version 3.1.9.2) [32,33]. Assuming a small effect of 0.01 (partial *η*^2^), a conventional type-1 error rate of 0.05, and a correlation of 0.5 among the repeated outcome measures, the study will be able to detect such an effect at 80% power with 69 participants in each group. However, considering an attrition rate of up to 30% by the final measurement occasion, it will be necessary to recruit at least 99 people per group, so we will aim for a total sample size of at least 200. The projected attrition rate of 30% is based on the attrition rates reported in previous RCTs [23-25] that examined interventions to increase well-being in hospital staff. Additional power calculations show that the study will be able to detect effects as small as 0.04 (partial *η*^2^) even under the strictest nonsphericity correction and possible attrition of up to 65%.

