#### Depression, Anxiety, and Stress Scale–21-Item Version

The Depression, Anxiety, and Stress Scale–21-item version [35,36] is a 21-item questionnaire that measures psychological distress (ie, symptoms of depression, anxiety, and stress). Each item presents a statement with a 4-point response scale ranging from *did not apply to me at all* to *applied to me very much or most of the time*. The respondents are asked to answer each statement in terms of how much it has applied to them *over the past week*.

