### Primary and Secondary Outcomes

The primary outcomes for this RCT will be the participants’ levels of well-being (as measured by the COMPAS-W) and their levels of psychological distress (as measured by the Depression, Anxiety, and Stress Scale–21-item version). Thus, the primary outcomes will encompass both dimensions of mental health: mental well-being and mental illness. The secondary outcomes will be health and lifestyle habits, mood states, compassion (for oneself and others), mindfulness, work performance, and work engagement. Program attendance, resiliency resources, medical history, trauma, coping styles, and pandemic-related variables will serve as potential moderator variables along with demographic variables such as age, sex, ward, and occupation. The primary end point for the analysis will be the third measurement occasion (week 8), and the secondary end points will be the second and fourth occasions (week 4 and week 12).

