### Analysis

Missing values in the data set will be estimated via multiple imputation, and the initial analyses will be conducted on an intention-to-treat basis followed by per-protocol analyses to account for levels of treatment compliance (eg, program attendance). The data will be analyzed via a linear mixed model that will allow the group-by-time interaction effects to be estimated. It is hypothesized that levels of well-being will increase over time in the intervention condition relative to the active control condition. Similarly, it is hypothesized that levels of psychological distress (ie, symptoms of depression, anxiety, and stress) will decrease over time in the intervention condition relative to the active control condition. There may also be a group-by-time interaction effect on one or more of the secondary outcomes. For example, the intervention may promote increased compassion, mindfulness, or work engagement. Furthermore, any interaction effect may itself be moderated by a variable such as resilience or coping style (cf [9,31]).

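### COMPAS-W is asked over a different time frame at baseline than at follow-up, so its change from week 0 within an arm cannot be read as a change in well-being alone

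*Protocol article*

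**What the plan says.** The COMPAS-W Scale section changes the frame after baseline: "the instructions will be modified for the second, third, and fourth surveys to ask the respondents how they have felt". The reference period given in those three surveys is the preceding month. Only surveys 2 to 4 are named, so survey 1 keeps the scale's standard, general frame, which the same section introduces with the clause "The respondents are asked to answer the items in terms of how they feel *most of the time* but, in this study".

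Table 1 lists COMPAS-W at all four surveys. Primary and Secondary Outcomes names "levels of well-being (as measured by the COMPAS-W) and their levels of psychological distress" as the primary outcomes and week 8 as the primary end point. The Design section describes one between-group factor and one repeated-measure factor with four occasions. The Analysis section plans a linear mixed model with a group-by-time interaction, and states the aim thus: "It is hypothesized that levels of well-being will increase over time in the intervention condition relative to the active control condition". The Sample Size section assumes "a correlation of 0.5 among the repeated outcome measures", a single value for all pairs of occasions.

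For comparison, DASS-21 is answered for the past week and Brief COPE for the past month. Both are given at all four surveys, with no change of frame described.

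**The concern.** A rating of how one generally feels and a rating of the last month are different questions. People may score systematically higher or lower on one than on the other with no change in their well-being. Because the switch falls exactly between week 0 and every later survey, it is inseparable from time since baseline.

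Two things are at stake:

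- **Interpretation within an arm.** The Discussion hopes to show whether the program preserves or raises well-being. To tell those apart within the intervention arm, the baseline and later scores must answer the same question.
- **Precision.** A general rating may correlate less with a one-month rating than one-month ratings do with each other. The sample size rests on a common correlation of 0.5.

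**Working it through.** **1. The plan's own sample size.** Inputs from the Sample Size section: partial η² = 0.01, α = 0.05, correlation ρ = 0.5. From the Design section: 2 groups and m = 4 occasions.

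- f² = 0.01/0.99 = 0.0101.
- λ = f²·N·m/(1 − ρ) = 0.0101 × 138 × 4/0.5 = 11.15, with 3 and 408 degrees of freedom.
- Power is 80.6% at N = 138 (69 per group) and 79.9% at N = 136.
- Attrition: 69/(1 − 0.30) = 98.6, so 99 per group.

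The stated figures reproduce. They depend on the wording only through ρ.

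**2. Where a wording shift goes.** Let the past-month frame move the mean score in arm g by c_g. Then

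- observed change from week 0 in arm g = true change + c_g;
- between-arm difference in change = true difference + (c_intervention − c_control);
- change between any two of weeks 4, 8 and 12 = true change, because c_g cancels.

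A simulation with no true change and no treatment effect (69 per arm, SD 1, ρ = 0.5, 4,000 trials per row, equal shift in both arms) agrees. The shift sizes are assumed, since the article gives none.

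| Shift (SD) | Apparent within-arm change, week 0 to 8 | Between-arm difference in change | Rejection at nominal 5% |
|---|---|---|---|
| 0 | 0.00 | −0.001 | 5.8% |
| 0.2 | 0.20 | 0.003 | 5.4% |
| 0.5 | 0.50 | −0.001 | 5.4% |

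The rejection rate stays near 5% and does not rise with the shift.

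**3. What a lower baseline correlation would cost.** With unit variance at each survey:

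- change score: variance = 2(1 − ρ), which is 1.0 at ρ = 0.5 and 1.4 at ρ = 0.3 (40% more);
- baseline as covariate: variance = 1 − ρ², which is 0.75 and 0.91.

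Power follows from a two-sided t test with standard error √(variance × 2/69). Two inputs are assumed: the range 0.3 to 0.5 for ρ, and a week-8 difference of 0.485 SD, chosen because it gives about the planned power at ρ = 0.5.

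| ρ, baseline to week 8 | Change score | Baseline as covariate |
|---|---|---|
| 0.5 | 80.7% | 90.4% |
| 0.4 | 73.3% | 87.0% |
| 0.3 | 66.7% | 84.3% |

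**4. How far 0.485 SD matters.** The article's η² fixes a week-8 difference only once a time profile is assumed. The interaction variance is one quarter of the variance, over the four occasions, of the between-arm differences.

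- Step profile (0, d, d, d): 0.1875d²/4 = 0.0101, so d = 0.46.
- Linear profile (0, a, 2a, 3a): 1.25a²/4 = 0.0101, so a = 0.18 and the week-8 difference is 0.36.

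For ρ = 0.5 and then 0.3, change-score power is 77.2% and 62.8% at 0.46 SD, and 55.6% and 42.7% at 0.36 SD. With baseline as covariate it is 87.8% and 81.0%, and 67.9% and 59.5%. The level of power moves a good deal. The advantage of the covariate analysis at each ρ does not go away.

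**The case against.** The strongest reply is that the confirmatory question is comparative. The Objectives and the Analysis section both ask about the intervention arm relative to control, allocation is randomised within ward, and the article says that the surveys are identical in the two arms. A common shift then falls into the main effect of time and leaves the interaction alone. This stands. A reader might infer that the treatment effect is biased; the documents do not support that, because they give no reason for the same wording to act differently by randomised arm.

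A reader might also infer that the trial cannot describe any change in mental health within an arm. That too goes too far: weeks 4, 8 and 12 share one frame, and DASS-21 has one stated frame throughout.

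Nor do the documents show that the trial is underpowered because of the wording. They give no COMPAS-W correlation under either instruction, 0.5 is itself a planning value, and the true baseline correlation could exceed it. The power figures above are illustrations.

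Finally, the general frame at survey 1 has a use. The second main objective is to describe current well-being across the hospital, and the scale's own instruction suits that. The article does not give this as its reason, but it is a fair argument against rewording survey 1 midway. What the reply does not answer is that COMPAS-W change from week 0 remains open to misreading, and that the article does not warn against it.

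**Conclusion.** The point holds in a limited form. COMPAS-W change from week 0 within an arm, and the time effect involving week 0, cannot be attributed to well-being alone, because any wording shift enters them one for one. The size of that shift cannot be determined from the article.

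The planned between-arm contrast is unbiased provided the wording acts equally in both arms, which identical surveys and randomisation make plausible.

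A loss of precision is possible but not established. If the baseline-to-week-8 correlation were 0.3, a change-score analysis with an assumed 0.485 SD difference would have 67% power against 81% at 0.5. Baseline adjustment would hold it at 84%. The point does not threaten the trial's main comparison, but it is cheap to deal with and should be dealt with.

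**What to change.** In the Analysis section:

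- enter baseline COMPAS-W as a covariate, and model only weeks 4, 8 and 12 as repeated outcomes;
- name the between-arm contrast at week 8 as the primary test for COMPAS-W;
- state that COMPAS-W change from week 0 will not be interpreted within arms.

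This costs only model wording. The baseline score is already collected, the Design section already provides for covariates, and the change applies equally to the five wards already surveyed. At the assumed 0.485 SD it also raises power, from 81% to 90% at ρ = 0.5 and from 67% to 84% at ρ = 0.3.

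Using the past-month frame at survey 1 in the remaining wards is optional. It would align the four surveys for those participants, at the price of a survey change and an ethics notification. It would also split the hospital-wide baseline description in the second objective across two different questions, and the model would then need wave and wave-by-baseline terms.

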#### Resilience Research Centre Adult Resilience Measure

The Resilience Research Centre Adult Resilience Measure [34] is a 28-item questionnaire that measures resiliency resources (eg, *I know where to get help in my community*). Each item presents a statement with a 5-point response scale ranging from *not at all* to *a lot*. This scale does not specify a period but simply asks the respondents to what extent each statement describes them.

#### Depression, Anxiety, and Stress Scale–21-Item Version

The Depression, Anxiety, and Stress Scale–21-item version [35,36] is a 21-item questionnaire that measures psychological distress (ie, symptoms of depression, anxiety, and stress). Each item presents a statement with a 4-point response scale ranging from *did not apply to me at all* to *applied to me very much or most of the time*. The respondents are asked to answer each statement in terms of how much it has applied to them *over the past week*.

#### Abbreviated Profile of Mood States (Revised Version)

The revised version of the Abbreviated Profile of Mood States [37] is a 40-item list of adjectives describing positive and negative mood states (eg, vigorous or unhappy), with a 5-point response scale ranging from *not at all* to *extremely*. The respondents are asked to what extent each adjective describes how they feel *right now*.

#### Brief Coping Orientation to Problems Experienced

The Brief Coping Orientation to Problems Experienced scale [38] is a 28-item questionnaire that measures 14 specific coping styles across the broader categories of approach coping (eg, *I’ve been taking action to try to make the situation better*) and avoidant coping (eg, *I’ve been refusing to believe that it has happened*). The 14 subscales are named *active coping*, *planning*, *positive reframing*, *acceptance*, *humor*, *religion*, *using emotional support*, *using instrumental support*, *self-distraction*, *denial*, *venting*, *substance use*, *behavioral disengagement*, and *self-blame*. Each item presents a method of coping with a 4-point response scale ranging from *I haven’t been doing this at all* to *I’ve been doing this a lot*. The respondents are asked to answer each statement in terms of how much they have been using that coping style *in the past month*.

